**Methods:**

The Nitric Oxide on Extracorporeal Membrane Oxygenation in Neonates and Children (NECTAR) trial is an open-label, parallel-group, pilot randomized controlled trial to be conducted at a single center. Fifty patients who require ECMO support will be randomly assigned to receive either NO mixed into the sweep gas of the ECMO system at 20 ppm for the duration of ECMO or standard care (no NO) in a 1:1 ratio, with stratification by support type (veno-venous vs veno-arterial ECMO).

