### Sample Size

The NECTAR trial is a pilot RCT with the main focus on feasibility, safety, and exploration of efficacy. A sample size of 50 patients has been chosen in line with the recommendations for pilot studies that anticipate a medium effect size for a continuous primary outcome for the main trial [17].

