### Safety Outcomes

There will be a focus on sweep gas delivery failure related to NO administration. Specifically, an arterial oxygen saturation of less than 80 due to a sweep gas interruption related to NO administration or carbon dioxide control outside of 30 to 50 mm Hg due to NO administration will be recorded as a safety event. The methemoglobin (MetHb) levels during the time of ECMO will be measured, and events above 3% related to NO administration will be noted.

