### Statistical Analysis Plan

#### Analysis Plan

Descriptive statistics will be used to report the baseline characteristics of the total study cohort and each subgroup. The primary efficacy outcome measure investigating days free of ECMO will be analyzed using quantile regression incorporating treatment group and VA or VV support (stratification variable) as fixed effects, with the treatment group effect estimate and 95% CI reported (assuming the data is abnormally distributed). Exploratory subgroup analysis by cardiac, respiratory, and ECMO-assisted cardiopulmonary resuscitation support will be performed. Analysis of secondary outcomes includes comparisons of measurements and proportions, with confidence intervals of differences as the major method of presentation. The primary analysis will be by intention-to-treat. If appropriate, per-protocol analyses will be performed as well and compared to the intention-to-treat. Statistical significance will be set at the .05 level and no adjustment for multiple comparisons will be made, noting the exploratory nature of the analysis. CIs will be generated using quantile regression for abnormally distributed continuous data, a 2-sided *t* test for normally distributed data, and a test of 2 proportions for binary data.

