## Discussion

### Principal Findings

The NECTAR trial will be the first RCT to assess the effect of NO on bleeding, clotting, and inflammatory complications in neonates and children supported on ECMO. It will establish the feasibility and safety of the procedure to allow the design of a trial powered for patient-centered outcomes.

Children requiring ECMO support continue to have a very high mortality risk. Both bleeding and clotting events are significantly associated with mortality and morbidity in this group of patients, and—in combination with inflammatory activation—they continue to pose a challenge to which no therapeutic answer has been found to date. The addition of NO to the sweep gas to reduce bleeding, clotting, and inflammatory complications is a promising therapeutic approach that has so far only been tested in vitro, in historical comparisons, or in RCTs on cardiopulmonary bypass settings rather than ECMO. Given the anticipated high safety of the intervention, the approach has the potential to improve patient-centered short- and long-term outcomes.

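### The interval method named for binary outcomes, in its ordinary large-sample reading, is unreliable for rare, unequal events at about 25 children per arm

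*Protocol article*

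**What the plan says.** The protocol article assigns one interval method to each type of data in the Analysis Plan; for binary outcomes it is "and a test of 2 proportions for binary data". It names no exact, score or continuity-corrected version and does not provide for sparse or empty cells. For secondary outcomes, the same section compares measurements and proportions "with confidence intervals of differences as the major method of presentation". It adds: "Statistical significance will be set at the .05 level", without multiplicity adjustment and with the analysis described as exploratory.

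On size, the Sample Size section states: "A sample size of 50 patients has been chosen in line with the recommendations for pilot studies". The abstract gives the allocation as "in a 1:1 ratio, with stratification by support type".

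Safety is among the main study outcomes. The Safety Outcomes section counts "an arterial oxygen saturation of less than 80 due to a sweep gas interruption related to NO administration", carbon dioxide outside its range because of NO, and methemoglobin: "events above 3% related to NO administration will be noted". No event rate is given for any of these. The Principal Findings section expects few problems: "Given the anticipated high safety of the intervention".

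**The concern.** The large-sample interval for a difference in proportions estimates its standard error from the observed proportions. When an arm has no events, that arm contributes nothing to the standard error. When neither arm has an event, the standard error is zero and the interval shrinks to a point. With about 25 children per arm and events expected to be uncommon, such tables are likely.

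At stake is how the pilot reports rare harms. An interval that is too short, or has no width, can appear to rule out an excess risk that the data cannot rule out. The pilot is meant to inform a larger trial, so its uncertainty about rare harms should be shown at its true size.

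**Working it through.** **Inputs.** Total 50, ratio 1:1, so 50/2 = 25 per arm. Level .05, taken as two-sided, so z = 1.96. The protocol states no figure for binary outcomes that could be reproduced first. All event rates below are assumptions.

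**Formulas.**
- Wald: d ± z·√[p₁(1−p₁)/25 + p₂(1−p₂)/25], with d = p₁ − p₂ from the observed proportions.
- Newcombe: with Wilson limits (l, u) for each arm, lower = d − √[(p₁−l₁)² + (u₂−p₂)²] and upper = d + √[(u₁−p₁)² + (p₂−l₂)²].
- Exact coverage: sum the binomial probabilities over all 26 × 26 possible tables in which the interval contains the true difference.

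**No events in either arm.** Wald: the standard error is 0, so the interval is 0 to 0. The pooled z statistic is 0/0 and undefined. The Wilson upper limit for 0/25 is z²/(25 + z²) = 3.84/28.84 = 13.3%, so Newcombe gives −13.3 to +13.3 points. The exact (Clopper-Pearson) upper limit for one arm with 0/25 is 1 − 0.025^(1/25) = 13.7%.

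**Coverage of the nominal 95% Wald interval, 25 per arm.**

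| Assumed true rates, NO vs control | Wald coverage | Chance of no event in either arm |
|---|---|---|
| 4% vs 0% | 63.7% | 36.0% |
| 4% vs 1% | 70.8% | 28.0% |
| 5% vs 0% | 72.1% | 27.7% |
| 8% vs 0% | 87.3% | 12.4% |
| 8% vs 2% | 86.8% | 7.5% |
| 12% vs 0% | 81.3% | 4.1% |
| 2% vs 2% | 99.8% | 36.4% |
| 4% vs 4% | 98.8% | 13.0% |
| 40% vs 40% | 93.8% | about 0 |
| 40% vs 30% | 93.6% | about 0 |

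Newcombe coverage in the six unequal rare-event rows runs from 99.3% to 99.97%.

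**Direction of the misses.** At 4% vs 0% the interval lies wholly below the true excess in 36.0% of trials (all of them 0/25 vs 0/25, since 0.96^25 = 0.360) and wholly above it in 0.3%. At 12% vs 0% the figures are 18.1% and 0.7%; 1/25 vs 0/25 already has an upper limit of 11.7 points, below the true 12. Nearly all misses understate the excess.

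**A table where the methods disagree on zero.** For 4/25 vs 0/25, d = 0.16 and the standard error is √(0.16 × 0.84/25) = 0.0733. Wald is 0.16 ± 0.144, or 1.6 to 30.4 points. Newcombe is −0.4 to 34.7 points, and Fisher's exact p = 0.11.

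**Equal rates.** At 2% vs 2% the empty table counts as covered because the true difference is 0. The interval of zero width still conveys a certainty that 25 children per arm cannot give.

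**The case against.** - **Wald is not named.** This stands. A reader might infer that the plan prescribes the uncorrected normal-approximation interval; the text supports only that this is the ordinary meaning. A continuity correction would give ±4 points at 0/25 vs 0/25 and would repair some scenarios (4% vs 0%) but not others (72.2% at 5% vs 0%). The article does choose the method, however, so this is not merely detail left to a fuller document.
- **No between-arm interval is specifically promised for the safety events.** This also stands. The sentence on intervals of differences as the main presentation concerns secondary outcomes, whereas gas failure, carbon dioxide control and methemoglobin are main outcomes to be recorded or noted. The general sentence on binary data could cover them, but no more than that.
- **The 0% control rows compare little.** Largely right. Several safety events are defined as caused by or related to NO, so the control count is essentially zero by definition. A two-arm difference adds little to the NO-arm count, which argues for a one-arm interval there.
- **False positives are not general.** Right. The 4/25 vs 0/25 table might suggest that the method often declares spurious differences. With equal true rates the Wald interval excludes zero in only 0.2% of trials at 2%, 1.2% at 4%, 4.1% at 8% and 4.9% at 10%.
- **The trial is an exploratory pilot with DSMB oversight.** This lowers the severity but does not make the interval correct.

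**Conclusion.** The point holds in a limited form. Read in the ordinary way, the named method under-covers for rare outcomes whose true rates differ between arms: 63.7% to 87.3% over assumed pairs from 4% vs 0% to 12% vs 0%, against a nominal 95%. It collapses to zero width when neither arm has an event. The misses almost all understate an excess in the NO arm.

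It would go too far to conclude that all binary analyses in the plan are unsound. At assumed mortality-type rates coverage is 93.6% to 93.8%, and at equal low rates it exceeds 95%. Nor does the article show which outcomes will be rare. Seizures, for example, are a genuine two-arm comparison among the subanalyses, but no rate is given for them.

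The conclusion rests on the large-sample reading of the phrase, on 25 children per arm, and on the assumed rates. Severity is minor to moderate, because the analysis is exploratory and no decision rule depends on these intervals.

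**What to change.** In the Analysis Plan, replace the phrase on binary data with three short statements:

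1. Risk differences for binary outcomes are reported with a score-based 95% interval (Newcombe or Miettinen-Nurminen; name one), including when one or both arms have no events.
2. Where cells are sparse, by a criterion stated in advance, the p value comes from Fisher's exact test.
3. For safety events that are defined as NO-related, the NO-arm count is reported with an exact (Clopper-Pearson) interval. For example, 0/25 is reported with an upper limit of 13.7%.

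The cost is a line or two of text and standard software options; check beforehand that the chosen routine returns limits for zero-event tables. No data collection or sample size changes. The downside is that intervals for rare events become wider and conservative: Newcombe coverage is about 99% or more in the unequal rare-event scenarios above. If a score or exact method was intended all along, the same edit says so.

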#### Long-term Outcomes

Neurodevelopmental and functional outcomes (using phone interviews and web-based questionnaires) will be documented at baseline (assessment of premorbid function during PICU admission) using the test battery described in Table 1. Assessments will focus on neurodevelopment, quality of life, executive functioning, adaptive behaviors, functioning, and parental outcomes. Assessments will occur at 6 and 12 months post cannulation. The following will be used for children younger than 5 years (for respective neurodevelopmental assessment areas): (1) ages and stages questionnaire, (2) pediatric emotional distress scale, and (3) behavior rating index of executive functioning for preschoolers. For all other children (and other neurodevelopmental function assessments), the following will be used: (1) strengths and difficulties questionnaire, (2) children’s revised impact of events scale, (3) vineland adaptive behavior scale, (4) pediatric cerebral performance category, (5) pediatric outcome performance category, and (6) pediatric quality of life inventory. For parental outcomes, the Kessler scale, as well as the Primary Carer – Post Traumatic Stress Disorder and Parenting Stress Index – Short Form will be used.

The neurodevelopmental outcomes will be reported separately from the main study.

**Table 1 table1:** Long-term outcome measures at 6 and 12 months after pediatric intensive care unit discharge.

Measure	<5 years of age	≥5 years of age
Neurodevelopment	Ages and Stages Questionnaire (ASQ)	Strengths and Difficulties Questionnaire (SDQ)
Quality of life	Pediatric Quality of Life Inventory	Pediatric Quality of Life Inventory
Distress	Pediatric Emotional Distress Scale (2-4 years) (PEDS)	Children’s Revised Impact of Events Scale (≥5 years) (CRIES)
Executive functioning	Behavior Rating Index of Executive Functioning for Preschoolers (2-4 years) (BRIEF-P)	Behavior Rating Index of Executive Functioning (≥5 years) (BRIEF)
Adaptive behavior	Vineland Adaptive Behavior Scale (VABS)	VABS
Functioning	Functional Status Score (FSS), Pediatric Cerebral Performance Category (PCPC), and Pediatric Outcome Performance Category (POPC)	FSS, PCPC, and POPC
Parent outcomes	Kessler (K6), Primary Carer – Post Traumatic Stress Disorder (PC-PTSD), and Parenting Stress Index – Short Form (PSI-4-SF)	K6, PC-PTSD, and PSI-4-SF

### Adverse Events

Given the severity of the underlying disease leading to the requirement for ECMO, patients are expected to have a high rate of adverse events unrelated to the study intervention. Events that are in the expected range of adverse events during standard treatment will therefore not be reported as related to the study intervention, as previously described [19]. Adverse events that are likely related to the study intervention will be reported. Adverse events likely related to NO delivery during ECMO support, such as failure to deliver sweep gas to the oxygenator, poor patient carbon dioxide control due to sweep gas failure, and increased MetHb (MetHb >3%) at any of the blood gas sampling points, will be reported [11,12]. Death will be reported as an adverse event and will be assessed as to whether it may be related to the study intervention. The study team, together with the treating physician, will assess each patient’s case and make an initial assessment of whether death occurred due to the intervention. The final assessment is to be confirmed with the DSMB.

## Discussion

### Principal Findings

The NECTAR trial will be the first RCT to assess the effect of NO on bleeding, clotting, and inflammatory complications in neonates and children supported on ECMO. It will establish the feasibility and safety of the procedure to allow the design of a trial powered for patient-centered outcomes.

Children requiring ECMO support continue to have a very high mortality risk. Both bleeding and clotting events are significantly associated with mortality and morbidity in this group of patients, and—in combination with inflammatory activation—they continue to pose a challenge to which no therapeutic answer has been found to date. The addition of NO to the sweep gas to reduce bleeding, clotting, and inflammatory complications is a promising therapeutic approach that has so far only been tested in vitro, in historical comparisons, or in RCTs on cardiopulmonary bypass settings rather than ECMO. Given the anticipated high safety of the intervention, the approach has the potential to improve patient-centered short- and long-term outcomes.

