### Limitations

The patient group requiring ECMO is very heterogeneous, and due to the pilot study size, achieving a normal distribution of risk factors in the 2 study groups may be unlikely. In addition, this pilot trial is not powered to assess associations between the intervention and clinical outcomes such as ECMO-free survival. It is designed to test the feasibility, safety, and efficacy of such an intervention and the conduct of such a study while exploring clinical and laboratory data in relation to the study groups.

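### The Discussion says the pilot will establish safety, but about 25 exposed children can only give a preliminary estimate: 0/25 NO-attributed events still allows a true rate of 11.3%

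*Protocol article*

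**What the plan says.** Under Principal Findings in the Discussion, the article says of the trial: "It will establish the feasibility and safety of the procedure to allow the design of a trial powered for patient-centered outcomes". The Limitations concede a lack of power for clinical outcomes, with ECMO-free survival as the example. They then add: "It is designed to test the feasibility, safety, and efficacy of such an intervention". Safety is not named in the power caveat.

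On size, the abstract states "Fifty patients who require ECMO support will be randomly assigned to receive either NO mixed into the sweep gas" or "standard care (no NO) in a 1:1 ratio, with stratification by support type". The Sample Size section explains: "A sample size of 50 patients has been chosen in line with the recommendations for pilot studies that anticipate a medium effect size". That recommendation concerns a continuous primary outcome for the main trial, not the precision of a safety rate.

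The Safety Outcomes section defines events by attribution. One is "an arterial oxygen saturation of less than 80 due to a sweep gas interruption related to NO administration". Carbon dioxide outside 30 to 50 mm Hg counts when it is due to NO, and methemoglobin above 3% when it is related to NO. The Adverse Events section likewise treats gas delivery failure, poor carbon dioxide control from such failure, and raised methemoglobin as events likely related to NO delivery.

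The Analysis Plan section presents secondary outcomes "with confidence intervals of differences as the major method of presentation". It generates intervals for binary data from a test of two proportions, and says: "Statistical significance will be set at the .05 level and no adjustment for multiple comparisons will be made".

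**The concern.** The verb in the Discussion promises a property that the design does not have. Establishing safety means ruling out a rate of harm that would matter. With about 25 exposed children, even a clean record leaves a substantial event rate possible.

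The planned interval does not make this visible. Events that must be related to NO essentially cannot occur in the standard-care arm. A two-arm difference therefore adds a control count that is zero by definition, and with few events the usual large-sample interval is too narrow or has no width.

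The same sentence makes safety part of the basis for designing a larger trial in critically ill neonates and children. Readers of the pilot should be able to see which event rate was excluded and which was not.

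**Working it through.** **Inputs from the article.** N = 50 and 1:1 allocation (abstract, Methods), so about 50/2 = 25 exposed to NO. Safety events are attributed to NO (Safety Outcomes; Adverse Events). Intervals for binary data come from a test of two proportions (Analysis Plan).

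**The article's own figure.** The 50 patients rest on a cited pilot-study recommendation. No inputs are given from which the number could be rebuilt, so it is neither reproduced nor disputed here.

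**Step 1: exact upper bound on the NO-arm rate.** The unit is the exposed child with at least one event. The one-sided 95% Clopper-Pearson bound is the rate p at which P(X ≤ x) = 0.05 for n = 25.

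- x = 0: (1 − p)^25 = 0.05, so p = 1 − 0.05^(1/25) = 0.113.
- x = 1: (1 − p)^25 + 25p(1 − p)^24 = 0.05 gives p = 0.176. Check: 0.008 + 0.042 = 0.050.
- x = 2: adding 300p²(1 − p)^23 gives p = 0.231. Check: 0.001 + 0.011 + 0.038 = 0.050.

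| Events in 25 | One-sided 95% upper bound | Two-sided 95% upper limit |
|---|---|---|
| 0 | 11.3% | 13.7% |
| 1 | 17.6% | 20.4% |
| 2 | 23.1% | 26.0% |

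**Step 2: sensitivity to the number exposed.** Blocking and re-randomisation of second runs can shift the 25 a little. With zero events, the one-sided bound is 12.2% for 23 exposed and 10.5% for 27.

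**Step 3: exposure that zero events would need.** To exclude a rate m at one-sided 95%, n is the smallest integer at or above ln 0.05 / ln(1 − m). This gives 29 children for 10%, 59 for 5%, 99 for 3% and 149 for 2%. The article names no rate to exclude, so these values of m are illustrative.

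**Step 4: what the planned interval shows.** The article does not name the form of the two-proportion interval. Take the common Wald form, with the control count at zero because of the event definition.

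- 0/25 vs 0/25: the standard error is √(0 + 0) = 0, so the interval has no width.
- 1/25 vs 0/25: the standard error is √(0.04 × 0.96/25) = 0.039. The upper limit is 0.04 + 1.96 × 0.039 = 11.7%, against 20.4% exact.
- 2/25 vs 0/25: the standard error is √(0.08 × 0.92/25) = 0.054. The interval is 0.08 ± 0.106, or −2.6% to 18.6%, against an exact upper limit of 26.0%.

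A score-based (Newcombe) interval for 0/25 vs 0/25 runs from −13.3 to +13.3 points. Its upper end is close to the exact 13.7%. Its lower half describes a benefit that the event definition does not allow.

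**The case against.** The strongest objection is that this is one loose verb in a Discussion. Elsewhere the wording is measured: the abstract's Objective speaks of testing safety, its Conclusions of investigating it, and the final Conclusions of informing a definitive trial. The sentence itself limits the purpose to designing the next study. Oversight is described, with an independent data and safety monitoring board that includes a statistician, at least four meetings, and the option to advise termination. All of this stands, and it keeps the point small. It does not give 25 exposed children more precision, and the milder wording elsewhere shows that the Discussion sentence is out of line.

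Three stronger readings are tempting, and the documents do not support them.

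- **Safety will be concluded from a non-significant test.** A reader might infer this from the .05 level. The article never says so, and it makes intervals the main form of presentation. Because the events are attributed to NO, calculations of two-arm power do not fit them either.
- **A record of zero events is the expected result even under harm.** It is not. The chance of no events is 0.95^25 = 28% at a true rate of 5%, and 0.90^25 = 7% at 10%. Zero events would be informative, but only down to about 11%.
- **The lack of a safety margin or stopping boundary is itself an error.** A condensed article can leave these to the full protocol, the SAP or the monitoring board's charter, none of which is shown.

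Continuous methemoglobin levels can also be estimated more precisely than rare events, and the bounds above do not apply to them. Death is reported whether or not it is related to NO, so a between-arm interval remains meaningful there.

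**Conclusion.** The point holds in limited form. The claim to establish safety goes beyond what about 25 exposed children can show. Zero NO-attributed events would exclude only rates above 11.3% (one-sided 95%). One event would exclude only rates above 17.6%, and two events only rates above 23.1%. For these outcomes the planned two-proportion interval is the wrong summary: in its Wald form it has no width at zero events, and its upper limit is too low at one or two.

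This rests on four assumptions: about 25 children exposed (23 to 27 changes little), one contribution per child, events counted per child, and a control count of zero because attribution to NO is part of the definition. Which rate would be tolerable is a clinical judgement that the article does not state and this review does not supply. The pilot's size does not need to change on this account.

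**What to change.** Two changes of text:

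1. In Principal Findings, replace the promise to establish feasibility and safety with: *will estimate the feasibility and provide preliminary safety data*, keeping the stated purpose of informing a later trial.
2. In the Analysis Plan, add: *For each safety event attributed to NO, the proportion of NO-arm children affected will be reported with its exact (Clopper-Pearson) one-sided 95% upper bound. The safety conclusion will be worded as the event rate excluded; for example, 0/25 excludes rates above 11.3%.*

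If the full protocol, SAP or monitoring board charter already holds a safety criterion, the second addition should refer to it.

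The cost is one extra interval per safety outcome and a less favourable stated claim. No further patients, data or clinical changes are needed.
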